### Methodological limitations

This study follows all the Consolidated Standards of Reporting Trials (CONSORT) recommendations, but participants cannot be blinded due to the intervention characteristics. However, the investigator who analyses the data will be blinded.

The acute effect of the high or low glycaemic index breakfast on the study variables may be influenced by conditions that cause endothelial dysfunction such as hypertension, diabetes or dyslipidaemia. Therefore, subjects with CVD, hypertension, diabetes or dyslipidaemia will be excluded.

Attempts to standardise food intake prior to experimental trials will not be made. However, participants will be asked to maintain stable dietary habits.

## Discussion

There is accumulating evidence that postprandial glycaemic response is associated with cognitive and vascular function [18, 23]. To our knowledge, the postprandial effects of high and low glycaemic index (GI) breakfasts on vascular parameters and cognitive performance have not been previously concurrently investigated.

Contrasting results have been reported about the effect of breakfast on vascular function and haemodynamic parameters [21, 22]. In this project, we expect to demonstrate that the lower glycaemic response to a low GI breakfast will have a greater lowering effect on measures of vascular function relative to a high GI breakfast.

Secondly, based on the findings of previous studies conducted on children and adolescents [26–30, 32], we hypothesise that we will see similar effects in healthy young adults. Thus, we expect that the lower glycaemic response to a low GI breakfast will have a positive impact on immediate and delayed verbal memory and verbal fluency, while the corresponding higher glycaemic response to a high GI breakfast will positively affect attention, processing speed and working memory.

Therefore, according to our hypothesis, the results of the current study may explain the influence of GI on cognitive and vascular function. Moreover, given the high worldwide prevalence of cardiovascular disease and its close relationship with cognitive decline, it would be interesting to know how the vascular parameters and cognitive processes are affected by the type of breakfast consumed. This could be employed for the design of novel lifestyle and dietary interventions.

Finally, our results may provide tools for adapting breakfast composition to the type of task to be performed and consequently for improving work performance.

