#### Nutritional composition of each intervention arm

The nutritional composition of each intervention arm is described as follows:Control condition (BF-1):This will consist of 350 mL of water served at room temperature.High glycaemic index breakfast (BF-2):This will consist of 350 mL of water served at room temperature, 200 mL of grape juice (with 569 kJ/136 kcal), 40 g of white bread (2 slices of 218 kJ/52 kcal each) and 29 g of strawberry jam (with 313 kJ/75 kcal), providing a total of 1318 kJ/315 kcal. The nutrient composition of this meal is 72.0 g (91.4 %) carbohydrate, 0.9 g (2.6 %) fat, 3.9 g (5 %) protein and 1.6 g (1 %) fibre, with an overall GI of 64.0.Low glycaemic index breakfast (BF-3):This will consist of 350 mL of water served at room temperature, a 150-g apple (with 339 kJ/81 kcal), a 125-g low-fat natural yogurt (with 234 kJ/56 kcal), 3 shelled walnuts (with 163 kJ/39 kcal per unit) and 17.5 g of 72 % dark chocolate (with 427 kJ/102 kcal), supplying a total of 1489 kJ/356 kcal. The nutrient composition of this meal is 31.5 g (35.4 %) carbohydrate, 19.9 g (50.3 %) fat, 9.7 g (10.9 %) protein and 6.0 g (3.4 %) fibre, with an overall GI of 29.4.

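### The two breakfasts differ in macronutrients and in every food as well as in GI, so the trial can compare two whole breakfasts but cannot attribute a difference to GI

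*Protocol article*

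**What the plan says.** Nutritional composition of each intervention arm fixes one high GI and one low GI meal for all participants.

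- **High GI meal:** grape juice, white bread and strawberry jam, "providing a total of 1318 kJ/315 kcal". It contains "72.0 g (91.4 %) carbohydrate, 0.9 g (2.6 %) fat" and "3.9 g (5 %) protein and 1.6 g (1 %) fibre", "with an overall GI of 64.0".
- **Low GI meal:** apple, low-fat yogurt, walnuts and dark chocolate, 1489 kJ/356 kcal. For this meal the section states "The nutrient composition of this meal is 31.5 g" of carbohydrate, with 19.9 g fat, 9.7 g protein, 6.0 g fibre and a GI of 29.4.

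The Discussion expects that "the lower glycaemic response to a low GI breakfast will have a greater lowering effect on measures of vascular function" relative to the high GI breakfast, and then states that "the results of the current study may explain the influence of GI on cognitive and vascular function". The Discussion paragraph of the Abstract likewise ascribes differences in glucose response to the GI of the breakfast, and links them to vascular and cognitive effects.

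Methodological limitations covers blinding, excluded conditions and diet before the visits. It says nothing about the composition of the meals.

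**The concern.** GI describes how fast a carbohydrate is absorbed; the Background defines it so. It does not describe how much carbohydrate a meal contains, nor its fat, protein or fibre. To learn what GI does, the rest of the meal would have to be held roughly constant, and here it is not.

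The Background itself gives reason to think that this matters. It singles out the carbohydrate content of a meal as altering glucose, insulin and AIx, and AIx is the primary outcome. It also notes that effects of other macronutrients on vascular function have been studied.

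At stake is what a result would mean. A difference between the breakfasts could come from GI, from the amount of carbohydrate, from fat or from another component, and the data could not say which. The Discussion wants the results to inform dietary interventions and work performance, so a wrong attribution could be passed on as advice about GI.

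**Working it through.** **1. Are the stated compositions reliable?** Item energies, from Nutritional composition of each intervention arm:

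- High GI: 569 + 2 × 218 + 313 = 1318 kJ; 136 + 2 × 52 + 75 = 315 kcal.
- Low GI: 339 + 234 + 3 × 163 + 427 = 1489 kJ; 81 + 56 + 3 × 39 + 102 = 356 kcal.

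Both totals reproduce. For the shares of energy, assume 4 kcal/g for carbohydrate and protein, 9 for fat and 2 for fibre (the protocol does not give factors):

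- High GI: carbohydrate 4 × 72.0 / 315 = 91.4 %; fat 9 × 0.9 / 315 = 2.6 %; protein 4 × 3.9 / 315 = 5.0 %; fibre 2 × 1.6 / 315 = 1.0 %.
- Low GI: carbohydrate 4 × 31.5 / 356 = 35.4 %; fat 9 × 19.9 / 356 = 50.3 %; protein 4 × 9.7 / 356 = 10.9 %; fibre 2 × 6.0 / 356 = 3.4 %.

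All agree with the protocol to rounding. The differences in composition are therefore intended features of the meals, not misprints.

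**2. How far do the meals differ?**

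| Component | High GI | Low GI | High − low | Larger ÷ smaller |
|---|---|---|---|---|
| GI | 64.0 | 29.4 | +34.6 | 2.18 |
| Carbohydrate, g | 72.0 | 31.5 | +40.5 | 2.29 |
| Fat, g | 0.9 | 19.9 | −19.0 | 22.1 |
| Protein, g | 3.9 | 9.7 | −5.8 | 2.49 |
| Fibre, g | 1.6 | 6.0 | −4.4 | 3.75 |
| Energy, kJ | 1318 | 1489 | −171 | 1.13 |

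Apart from the 350 mL of water, no food appears in both meals.

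**3. Can an analysis separate GI from the rest?** Let D be the mean difference in an outcome, high minus low GI breakfast. Each component takes one value in each meal, the same for everyone, so each is an exact function of which breakfast was eaten. The data give one number, D, and at least six components compete to explain it.

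Take D = 5 AIx points, the difference used under Sample size. The following descriptions fit equally well:

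- 5 / 34.6 = 0.145 points per unit of GI;
- 5 / 40.5 = 0.123 points per gram of carbohydrate;
- 5 / (−19.0) = −0.263 points per gram of fat;
- any mixture of these with the other components.

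The general linear model under Statistical analysis cannot choose among them, because adding a composition covariate to a model that already contains breakfast adds no information. The water condition does not help either: it adds a comparison of each meal with no meal, not a meal in which GI varies while the rest is fixed. Randomisation and crossover balance participants, not the components of the meals.

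**The case against.** The strongest reply is that the protocol compares breakfasts and largely says so. This stands on several points.

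- A reader might infer that the objectives attribute the effect to GI. They do not. The primary objective under Objectives concerns low and high GI breakfasts, which the design answers if these are read as whole meals. The secondary objective already calls the glucose analysis an association, and Statistical analysis plans correlations for it. Neither needs rewording.
- Statistical analysis compares the three types of breakfast. No planned step estimates a GI effect, so the analysis is not at fault.
- A reader might say that the meals differ far more in carbohydrate than in GI. The ratios are 2.29 and 2.18, practically the same. The clearly larger ratio is for fat, and part of its size comes from the small 0.9 g denominator; the gap of 19.0 g is substantial all the same.
- A reader might compute glycaemic load and assign a percentage of the contrast to something other than GI. The protocol does not use glycaemic load, and such a split would say nothing about shares of an AIx or cognitive effect.
- The hypothesis runs through the glucose response, which the amount of carbohydrate helps to produce. For that hypothesis carbohydrate is not simply a nuisance. Fat, protein, fibre and the foods themselves still are.
- The Discussion sentence is hedged, and its neighbours speak of the type and composition of breakfast.

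The hedge does not rescue the attribution. It allows for uncertainty about the result, whereas the difficulty is that no result from these two meals could show an influence of GI as such. The Abstract makes the same attribution, and the limitations are silent on it.

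**Conclusion.** The point holds as a fault in the stated inference, not in the comparison. The trial can validly estimate the difference between these two breakfasts. It cannot attribute that difference to GI, because a GI contrast of 34.6 units comes with 40.5 g more carbohydrate, 19.0 g less fat, 5.8 g less protein, 4.4 g less fibre, 171 kJ less energy and an entirely different set of foods.

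The conclusion rests only on the compositions stated in the protocol and on every participant receiving the same two meals. It does not depend on glycaemic load, on any assumed effect of a particular food, or on the sample size. It does not show that GI has no effect, nor how much of any difference the other components would cause; the documents give no basis for either. No fuller analysis plan could change the conclusion, since it follows from the meals as fixed.

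**What to change.** Leave the meals, randomisation, outcomes and analysis unchanged, and change the wording in three places:

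1. **Discussion.** Remove the statement that "the results of the current study may explain the influence of GI on cognitive and vascular function". State the hypothesis and the conclusion as a difference between two specified breakfasts that differ in GI and in macronutrient and food composition.
2. **Abstract, Discussion paragraph.** Replace the attribution to GI with the same whole-breakfast wording.
3. **Methodological limitations.** Add that the two breakfasts are not matched for carbohydrate, fat, protein, fibre, energy or foods, so that an effect of GI cannot be separated from an effect of these.

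The report of results should use the same wording. The cost is editorial, with no effect on recruitment or visits. The downside is a narrower claim, about these two breakfasts rather than about GI in general.

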## Trial status

This trial is currently recruiting participants.

## Abbreviations

AIx: Augmentation index
BF: Breakfast
BGI: Breakfast glycaemic index
BP: Blood pressure
CAFE: Conduit Artery Function Evaluation
CBP: Central blood pressure
CHO: Carbohydrate
CREC: Clinical research ethics committee
CVD: Cardiovascular disease
DBP: Diastolic blood pressure
DQI: Diet Quality Index
EVIDENT: Lifestyles and Vascular Aging (study)
GI: Glycaemic index
HR: Heart rate
IBSAL: Institute of Biomedical Research of Salamanca
IPAQ: International Physical Activity Questionnaire
LOPD: Legislation on personal data protection
MET: Metabolic equivalent of task
PWV: Pulse wave velocity
REDIAPP: Network for preventive activities and health promotion
SBP: Systolic blood pressure
SEEDO: Spanish Society for the Study of Obesity
WAIS: Wechsler Adult Intelligence Scale
